**Table 2 Tab2:** **Summary of measures to be collected**

Primary outcome measures	Data collection instrument	Collection points
Physical functioning	HOOS and/or KOOS	0, 3, 12 months
	Timed “Up & Go” test	0, 3 months,
Physical activity	SQUASH	0, 3, 12 months
	ActiGraph GT3X tri-axial accelerometers	0, 3, 12 months
**Secondary outcome measures**		
OA related costs	Cost questionnaire	3, 6, 9, 12 months
Health related quality of life	EQ-5D	0, 3, 12 months
Self-perceived effect	7-point Likert scale	3, 12 months
Pain	NRS	0, 3, 12 months
Tiredness	NRS	0, 3, 12 months
Self-efficacy	Arthritis self-efficacy Scale	0, 3, 12 months
**Other measures**		
Age	Questionnaire	0 months
Sex	Questionnaire	0 months
Height	Questionnaire	0 months
Weight	Questionnaire	0, 3, 12 months
Educational level	Questionnaire	0 months
Location of OA	Questionnaire	0 months
Disease duration	Questionnaire	0 months
Presence of comorbidities	Questionnaire	0 months
Adherence	Completed web-modules	During intervention

#### Primary outcome measures

*Physical functioning* will be assessed subjectively with the subscale ‘function in daily living’ of the Hip OA Outcome Score (HOOS) [34] and/or the Knee Injury and OA Outcome Score (KOOS) [35], depending their affected joint. The HOOS and the KOOS assess 5 indicators: pain, symptoms, physical function, sport and recreation function and quality of life, in relation to patients’ hip or knee complaints. Each indicator is scored on a 5-point Likert scale (0 = extreme symptoms/problems; 4 = no symptoms/problems). A lower score indicates respectively more pain, symptoms, problems in physical functions, problems in sports and recreation activities and a lower quality of life. In addition, objectively physical functioning will be measured by the physical therapist with timed “Up & Go” test (TUG) [36]. In this easily administered test, the patient is requested to rise from an arm chair, walk three meters, turn, walk back again and sit down. Meanwhile, the physical therapist observes the patient and measures the time.

*Physical activity* will be measured subjectively with the SQUASH [37]. The questionnaire measures habitual PA during a normal week over the last few months. The total score is expressed as minutes per week. In addition, data can also be analysed according to whether the activity is light, moderate or vigorous. Objective PA will be measured through ActiGraph GT3X tri-axial accelerometers. Participants will be instructed to wear the monitor on a belt around their waist for five executive days [38], except during sleeping, showering or swimming. In addition, participants will be requested to fill out a short activity diary. This diary contains questions about wearing time, unusual activities and reasons for device removal. When accelerometers and diaries are returned by post, data can be downloaded, processed and subsequently analyzed. The widely accepted PA thresholds of Freedson et al. [39] will be used: 0–99 counts for sedentary activities, 100–1951 for light PA, 1952–5724 moderate PA, 5725–9498 for vigorous PA and 9499- max for very vigorous activities. The total time spent in light, moderate and vigorous PA will be summed and subsequently divided by the number of days worn to compute the daily average time spent in total activity. For analysis, data will be recorded at 1-minute intervals.

#### Secondary outcome measures

*Information on the patients’ healthcare utilization, (unpaid) productivity losses, and sports costs due to OA* will be gathered with four retrospective 3-month cost questionnaires that cover the full 12-months of the program. Healthcare utilization due to OA comprises of visits to a physical therapist, general practitioner, massage therapist, alternative therapist, medical specialist, as well as informal care, hospital care, the use of both prescribed and over the counter drugs and medical devices. Healthcare utilization will be valued using Dutch standards costs [40]. If these are unavailable, prices reported by professional organizations will be used. Medication use will be valued using unit prices derived from the “Royal Dutch Society of Pharmacy” [41]. Unpaid productivity losses will be valued in accordance with the “Dutch Manual of Costing” [40]. Paid productivity losses comprise of both sickness absence and presenteeism (i.e. reduced productivity while at work). Sickness absence will be valued in accordance with the “Friction Cost Approach” (FCA), with a friction period of 23 weeks and an elasticity of 0.8, using age- and gender-specific price weights [40]. The FCA assumes that production losses are confined to the “friction period” (i.e. time needed to replace a sick worker) and that a 100 percent loss of labour input corresponds with an 80 percent reduction in productivity (i.e. an elasticity of 0.8) [42]. The participants’ level of presenteeism will be measured using the “World Health Organization – Work Performance Questionnaire” as well as the “Productivity and Disease Questionnaire”, and valued using age- and gender-specific price weights [40, 43–45]. The cost of the e-Exercise intervention will be estimated using a bottom-up micro-costing approach [46].

*Health Related Quality of Life* will be measured with the EuroQol-5D (EQ-5D) [47]. This questionnaire comprises of 5 dimensions i.e., mobility, self-care, usual activities, pain/discomfort and anxiety/depression. Per dimension, patients are asked to indicate their health state on a 3-point Likert scale (1 = no problems; 3 = extreme problems). The questionnaire differentiates between 245 health states. These health states will be converted into utility units by using the Dutch tariff [48]. Utilities represent quality of life into a single number that ranges from 0 (death) to 1(full health). Quality adjusted life years (QALY’s) will subsequently be calculated by multiplying the participants’ health state utilities by the duration of time they spent in that particular health state.

*Self-perceived effect* will be assessed by a single question about the degree of change in osteoarthritis symptoms since their previous assessment. Patients will score this effect on a 7-point Likert scale (1 = much worse; 7 = much better). A higher score indicates a better self-perceived effect.

*Pain and tiredness* will be measured with a numeric rating scale (NRS; 0 is no pain/not tired and 10 is worst possible pain/very tired). Furthermore, pain will be assessed with the pain subscale of the HOOS and/or the KOOS [34, 35].

*Self-efficacy* will be measured by the Arthritis Self-efficacy Scale (ASES) [49]. Subscales for the ASES are pain, symptoms and physical functioning, the 19 statements can be scored on a 5 point-Likert scale (1 = fully disagree; 5 = fully agree). A higher score indicates more self-efficacy.

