### Measurements

Three online questionnaires (0, 3 and 12 months) will be used for data collection. Participants will receive an accelerometer for the measurement of objective PA (0, 3 and 12 months). The physical therapists will measure physical functioning objectively at baseline and post-treatment (3 months). In addition, online cost questionnaires will be sent (0, 3, 6, 9 and 12 months). We offer no financial incentives to complete questionnaires or to wear accelerometers. Table 2 gives a summary of all measures that will be collected.

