#### Effectiveness

To determine the short (baseline-3 months) and long term (baseline −12 months) effectiveness of e-Exercise on primary and secondary outcomes, multi-level modelling of repeated measures will be performed controlling for baseline values and relevant confounders such as age, OA location and gender. With multilevel modelling of repeated measures it is possible to correct on one side for dependency of observations within subjects and, on the other side, to take into account the variation between physical therapists [50, 51]. The three-level hierarchy will exist of repeated measurements (level 1), nested within patients (level 2), nested within physical therapists (level 3).

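### The 12-month self-perceived effect rating covers months 3 to 12, not the baseline-to-12-month period that the plan sets for long-term effects

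*Protocol article*

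**What the plan says.** Four statements in the Protocol article bear on this point.

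- **Reference point and scale.** Under Secondary outcome measures, self-perceived effect is "a single question about the degree of change in osteoarthritis symptoms since their previous assessment". It is an ordinal rating from 1 (much worse) to 7 (much better).
- **When it is collected.** Table 2 lists "Self-perceived effect 7-point Likert scale 3, 12 months". There is no month-0 entry.
- **What counts as an assessment.** The Measurements section says "Three online questionnaires (0, 3 and 12 months) will be used for data collection". Cost questionnaires are listed there separately, as an addition.
- **What is to be estimated.** The Effectiveness section opens with "To determine the short (baseline-3 months) and long term (baseline −12 months) effectiveness of e-Exercise on primary and secondary outcomes" and continues that "multi-level modelling of repeated measures will be performed controlling for baseline values and relevant confounders such as age, OA location and gender".

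The article gives this item no other reference point, no rule for combining its two ratings and no separate analysis.

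**The concern.** The research question is about both short-term (3-month) and long-term (12-month) effectiveness, and the Discussion counts the 12-month follow-up as a strength. A secondary outcome reported under the long-term heading should therefore compare the arms on what has happened since baseline.

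A transition item has no fixed zero: it measures change from whatever moment the question names. If that moment moves from baseline (at the 3-month visit) to month 3 (at the 12-month visit), the two ratings answer different questions, and only the first matches the stated contrast.

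At stake is how the 12-month result is read. Suppose e-Exercise patients improve more by month 3 and stay improved. Asked at 12 months how they have changed since the last assessment, they should tend to answer that little has changed. Reported as the baseline-to-12-month effect, that answer would suggest that the benefit had gone when it had been kept.

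**Working it through.** The plan states no figure for this outcome, so there is none to reproduce. The check compares the period that each rating covers with the period that the plan assigns to it.

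**Inputs**
- Outcome questionnaires at 0, 3 and 12 months (Measurements).
- Item collected at 3 and 12 months (Table 2).
- Reference point: the previous assessment (Secondary outcome measures).
- Planned contrasts: baseline to 3 months and baseline to 12 months (Effectiveness).
- Intervention length: 12 weeks (Abstract). The Measurements section itself treats month 3 as post-treatment.

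**Step 1: period covered = current visit − previous visit**

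| Visit | Period rated | Length | Planned contrast | Match |
|---|---|---|---|---|
| 3 months | 0 to 3 | 3 − 0 = 3 months | 0 to 3 | yes |
| 12 months | 3 to 12 | 12 − 3 = 9 months | 0 to 12 (12 months) | no |

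The 12-month rating misses 12 − 9 = 3 months, and these are the months that contain the treatment.

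**Step 2: what this does to the group contrast**

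Let d3 and d12 be the between-arm differences in symptom change from baseline at 3 and 12 months. The plan asks for d12. An item anchored at month 3 targets d12 − d3. The discrepancy is d12 − (d12 − d3) = d3, which is the whole short-term effect.

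The values below are assumptions, in standard deviation units of an underlying symptom score, chosen only to show direction:

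| Assumed d3 | Assumed d12 | Planned contrast (d12) | Item's contrast (d12 − d3) |
|---|---|---|---|
| 0.4 | 0.4 (fully kept) | 0.4 | 0.0 |
| 0.4 | 0.2 (half kept) | 0.2 | −0.2 |
| 0.4 | 0.0 (lost) | 0.0 | −0.4 |
| 0.2 | 0.4 (still growing) | 0.4 | 0.2 |
| 0.0 | 0.4 (late only) | 0.4 | 0.4 |

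The two contrasts agree only when d3 = 0, that is, when there is no short-term effect.

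**Step 3: does the model repair it?**

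A repeated-measures model with a separate group contrast at each visit keeps the two ratings apart, but its 12-month contrast still estimates change since month 3. Adjustment for the baseline value is not available for this item, because a change rating has none and Table 2 lists none.

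**Step 4: after re-anchoring**

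With the same pre-treatment anchor at both visits, the ratings cover 0 to 3 months and 0 to 12 months. Both match the Effectiveness section.

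**The case against.** The case on the other side has several parts.

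- **Change since the last visit is a legitimate measure.** This stands. Both ratings give valid randomised comparisons of their own intervals, and in the half-kept example the item would correctly report relative worsening since month 3. What fails is describing that result as the baseline-to-12-month effect.
- **The exact questionnaire item is not shown.** This also stands. The article gives a one-sentence description, and the item in use may already refer to the start of treatment. In that case the description is wrong and needs correcting. Either way, the two statements in the article do not fit together; this is a conflict in what is stated, not a detail left to a fuller document.
- **The harm is limited.** This stands too. Pain, tiredness, self-efficacy, quality of life and self-reported physical functioning are all measured at 0, 3 and 12 months and support a direct baseline-to-12-month comparison. A flat self-perceived rating beside a maintained pain benefit could be recognised as maintenance. The sample size basis and the economic evaluation do not use this item.

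Three stronger readings are tempting, but the document does not support them.

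- A reader might infer that the 12-month rating could refer to month 9, because "online cost questionnaires will be sent (0, 3, 6, 9 and 12 months"). The Measurements section lists these questionnaires apart from the three outcome questionnaires, so on the article's own usage the previous assessment is month 3. How a patient might read the question is conjecture.
- A reader might infer that the two ratings cannot be analysed in one repeated-measures model. They can, with visit-specific contrasts. Only a single effect averaged over both visits would mix unlike quantities, and the article does not say that one is planned.
- A reader might infer that all of a maintained effect is demonstrably lost. That follows only from treating a 7-point ordinal rating as an exact difference of symptom scores. The examples show direction, not an expected size.

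**Conclusion.** The point holds for the 12-month value. As described, that rating covers months 3 to 12, omits the treatment period and does not estimate the long-term contrast that the Effectiveness section sets for secondary outcomes. If there is a short-term benefit, the 12-month rating will tend to understate what has been kept since baseline, by an amount that grows with the short-term effect. The document gives no basis for putting a number on this.

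The scope is narrow: one single-item secondary outcome at one visit. The 3-month rating is correctly anchored, because its previous assessment is baseline, and the primary outcomes are untouched.

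The conclusion assumes that the article describes the item's wording accurately and that the previous assessment means the previous outcome questionnaire.

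**What to change.** **If the wording can still be changed:** anchor the item at both visits to the same moment, for example *since before the start of treatment*. Analyse it with a separate group contrast at 3 and at 12 months, and state that no baseline covariate applies because the item has no baseline value. This costs one phrase in an online questionnaire and one sentence in the analysis section. The real downside is recall: at 12 months patients would look back 12 months rather than 9.

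**If the wording is already in use:** keep it, so that responses stay comparable across patients. State that the 12-month rating estimates change from month 3 to month 12, and report it under that label rather than as the baseline-to-12-month effect. This costs only a change of text.

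**If the item in use already refers to the start of treatment:** correct the description under Secondary outcome measures.

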#### Other measures

*Adherence* will be measured objectively by quantitative data about usage which is automatically stored on the backend of the website. Usage is defined as completed week modules. Subjective adherence is measured by a questionnaire about patients’ adherence to the Graded Activity modules and Strength & Stability exercises (frequency and intensity).

*Content of physical therapy sessions* will be measured trough registrations forms, developed by the researchers. The registrations forms collect information about the adherence and content of the sessions.

*Patient characteristics* i.e. age, sex, height, weight, educational level, location of OA, disease duration and the presence of comorbidities will be assessed at baseline.

### Sample size

The power calculation is based on a previous multicenter cluster RCT study among patients with hip and/or knee OA [27] and performed for the primary outcome measure physical functioning (power 0.8; alpha 0.05). In this current RCT study, the target sample size will be 200 participants to detect a small to medium effect size (0.2-0.4) in physical functioning at a 2-sided significance level of 0.05 and anticipating on maximum loss to follow up of 20%.

### Statistical analysis

Descriptive statistics will be used to describe the main characteristics of the study population and to explore baseline comparability (frequencies, t-test, Chi-square). Primary baseline variables between the response and the non-response group will be performed in order to investigate selective attrition. The primary analysis will be performed according to the intention-to-treat principle. In addition, per-protocol analyses that include only adherent patients of the intervention group and the entire control group will be performed. For all analyses, a two-tailed significance level of p < 0.05 is considered to be statistically significant. All analyses will be carried out with the statistical package STATA.

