The internet has created new possibilities to combine face-to-face care with online care, called blended healthcare [17]. The partial substitution of a web-based intervention for exercise therapy sessions is hypothesized to result in a (cost)-effective intervention in many ways. In the first place, a blended intervention will result in lower costs since the average number of physical therapy sessions for patients with OA will decrease. A second advantage of a blended intervention is the 24/7 online support for exercises at home. Support in exercises at home is important since adherence to self-directed exercise is a common problem in exercise therapy [18, 19]. Research highlighted the importance of adherence to exercises at home, since this positively influences treatment effects on pain and physical functioning [19]. Third, a well-designed web-based intervention in which patients’ can report their experiences with home exercises provides physical therapists information about patients’ individual needs for guidance.

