### Study procedure

Physical therapists willing to participate in the study will be screened on in- and exclusion criteria by a researcher (CK). Cluster randomization will be performed at the level of the participating physical therapy practices that will randomly be assigned to the intervention (e-Exercise) or the control group (usual care) by means of a computer-generated random sequence table. Physical therapists will receive a half day training about e-Exercise and the study procedure (intervention group) or about practicing according to the “KNGF guideline OA hip-knee” [10] and the study procedure (control group). Physical therapists will inform eligible patients about the study and screen them on in- and exclusion criteria. All suitable patients will be stimulated to contact the research team by telephone, e-mail or reply card. After an informative phone call with one of the researchers (CK or DB), interested patients will receive a letter about the trial and a request to complete an informed consent form. Patients recruited by the additional recruitment strategies (i.e. advertisements in newspapers and flyers from the general practitioner) will be informed by the researchers before they visit their physical therapist. Physical therapists in both groups will be asked to record the content of their treatment on a registration form. During the study period, both patient groups will continue their medication and usual care managed by other caregivers.

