Although the study is well-considered, we take into account potential operational issues. First challenge is the recruitment of sufficient numbers of physical therapists. Since e-Exercise is characterized by fewer physical therapy sessions, physical therapists will receive less reimbursement from health insurances compared to usual care. To deal with this challenge, accreditation points for participating physical therapists will be supplied in order to make study participation more attractive. Another incentive is that physical therapists keep their access to the website after the study is finished. The second challenge is the non-usage of the web-based part of e-Exercise. Previous studies have indicated that participants in online interventions are less motivated and feel less pressure to continue compared to traditional face-to-face interventions [59]. However, in order to stimulate website usage, we will incorporate email reminders into the program. But most importantly, since this study concerns a blended intervention, which is a combination of face-to-face contact with e-health, e-Exercise is expected to maximize adherence compared to self-guided internet interventions [17, 23].

There are several strengths in the design of this study. First, we elaborate on the study results of Joint2Move [24]. This intervention showed to be an effective web-based intervention for patients with OA of the hip and/or knee and will be the fundament for e-Exercise. Second, the primary outcome measurements PA and physical functioning will be measured subjectively (questionnaires) and objectively by means of accelerometers and the timed “Up & Go test”. Third, the 12-month follow-up will result in data about long-term effectiveness. The last strength is that e-Exercise will be evaluated in daily physical therapy practice, the setting in which the intervention will be implemented after the presented trial. Therefore, user experiences can be used in order to improve e-Exercise and to facilitate implementation.

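### The per-protocol analysis sets adherent e-Exercise patients against all controls, so it is not a randomised comparison and tends to favour e-Exercise if adherers have the better prognosis

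*Protocol article*

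**What the plan says.** The *Statistical analysis* section of the protocol article sets the main analysis: "The primary analysis will be performed according to the intention-to-treat principle". It then adds that "per-protocol analyses that include only adherent patients of the intervention group and the entire control group will be performed". The two-tailed 5% level is applied to all analyses, and nothing marks this one as exploratory.

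Under *Other measures*, objective adherence is website use: "Usage is defined as completed week modules". A patient questionnaire covers adherence to the graded activity modules and the strength and stability exercises. For the therapist forms the article says: "The registrations forms collect information about the adherence and content of the sessions". *Study procedure* has therapists in both groups record treatment content, but no adherence condition is set for controls.

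The effectiveness models work by "controlling for baseline values and relevant confounders such as age, OA location and gender". On allocation: "Cluster randomization will be performed at the level of the participating physical therapy practices".

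**The concern.** Module completion is observed after allocation and belongs to the e-Exercise programme. Removing low users from that arm while keeping the controls who would have been low users compares a selected group with an unselected one. No choice of module cut-off makes the two sides alike.

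The article itself expects exclusions: "The second challenge is the non-usage of the web-based part of e-Exercise". In the *Discussion* it links weak use of online programmes to lower motivation. Motivation is not among the named covariates and is not directly measured. The modules consist of graded physical activity and home exercises, and physical activity is a primary outcome. Choosing module completers therefore comes close to choosing patients on the outcome.

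At stake is the reading of a null intention-to-treat result printed beside a per-protocol result below 0.05. It could be taken to show that e-Exercise works when used, although selection alone may produce that pattern.

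**Working it through.** The plan gives no figure for this analysis, so there is none to reproduce. The yardstick is the effect size of 0.2 to 0.4 in *Sample size*.

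**Inputs**
- From the article: 200 patients in total, two-sided alpha 0.05.
- Assumed: 1:1 allocation (100 per arm), adherent share p from 0.9 to 0.5, and residual correlation rho from 0.1 to 0.3 between a latent adherence tendency and the outcome after adjustment. The article gives neither p nor rho.

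**Step 1: bias when the two treatments are equally effective.** The mean of the adherers exceeds the mean of the whole arm by (1 − p) × gap, where gap is the difference in mean outcome between adherers and non-adherers. With p = 0.5 and a gap of 0.4 SD this is 0.5 × 0.4 = 0.20 SD. With p = 0.6 and 0.2 SD it is 0.4 × 0.2 = 0.08 SD.

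In terms of correlation, with t the standard normal (1 − p) quantile and phi the normal density:

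bias = rho × phi(t)/p

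The factor phi(t)/p is 0.195, 0.350, 0.497 and 0.798 for p = 0.9, 0.8, 0.7 and 0.5.

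**Step 2: rejection rate with no true effect.** With L = phi(t)/p, the variance among adherers is v = 1 − rho² × L × (L − t), and SE = √(v/(100p) + 1/100). For p = 0.7 and rho = 0.2:
- L = 0.497 and t = −0.524, so v = 0.980.
- SE = √(0.980/70 + 0.01) = 0.155.
- Bias = 0.2 × 0.497 = 0.099 SD, and bias/SE = 0.64.
- The two-sided rejection rate is 0.098, of which 0.094 favours e-Exercise.

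Bias in SD, with two-sided type I error in brackets:

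| Adherent share p | rho = 0.1 | rho = 0.2 | rho = 0.3 |
|---|---|---|---|
| 0.9 | 0.019 (0.052) | 0.039 (0.058) | 0.058 (0.069) |
| 0.8 | 0.035 (0.056) | 0.070 (0.076) | 0.105 (0.109) |
| 0.7 | 0.050 (0.062) | 0.099 (0.098) | 0.149 (0.163) |
| 0.5 | 0.080 (0.075) | 0.160 (0.153) | 0.239 (0.291) |

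At rho = 0 the bias is zero and the error 0.05. At rho = −0.2 and p = 0.7 the bias is −0.099 SD. With 80 patients per arm, after the anticipated 20% loss, the biases are the same and the error runs from 0.052 to 0.243 over the table.

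Two limits apply. Clustering is ignored; allowing for it widens the standard error and lowers these error rates without changing the bias. The SD is that of the outcome after adjustment, so the comparison with the 0.2 to 0.4 target is approximate and the bias on the unadjusted scale is somewhat smaller.

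**Step 3: would a complier-average estimate be free of bias?** The intention-to-treat effect is p × tau_c + (1 − p) × tau_n, where tau_c and tau_n are the effects of allocation in adherers and non-adherers. Dividing by p gives

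estimate = tau_c + ((1 − p)/p) × tau_n

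The second term vanishes only if tau_n = 0. With an assumed tau_n of −0.2 SD it is (0.5/0.5) × (−0.2) = −0.20 SD at p = 0.5, (0.4/0.6) × (−0.2) = −0.13 SD at p = 0.6, and (0.1/0.9) × (−0.2) = −0.02 SD at p = 0.9.

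**The case against.** The strongest reply has four parts.

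- **The analysis is additional.** Intention-to-treat is primary, and neither the main result nor the sample size depends on the per-protocol set. This stands and limits the weight of the point. A reader might infer that the trial's main conclusion is biased; the article does not support that.
- **The direction is not assured.** A reader might infer that the analysis must show a benefit even if e-Exercise does nothing. It does so only on average, and only if a positive association between adherence and prognosis remains after adjustment. The *Background* remark on home-exercise adherence, "since this positively influences treatment effects on pain and physical functioning", describes an effect of exercising more. It does not show that adherers do better whatever treatment they receive. The *Discussion* also expects the blended format to raise adherence above that of self-guided internet programmes, so the high-adherence rows of the table, with small bias, belong in the range. All of this stands.
- **Keeping every control has a reason.** Usual care is defined as any physical therapist treatment, so a control patient has little protocol to breach. This explains the choice but does not restore comparability. Nor does it help that adherence might be defined by the questionnaire or the registration forms instead of modules: restricting one arm only would still break the randomised contrast. The lack of a stated cut-off is not counted, since an analysis plan may supply it.
- **The usual replacement has its own weakness.** The control is active physical therapy; the article cites an average of 17.1 sessions in patients with OA. A patient below a module threshold still gets e-Exercise face-to-face care of at most five sessions, not usual care. Allocation can then affect outcome without module completion, and Step 3 shows that the resulting bias can match the one being removed. This stands, so a complier-average estimate should supplement the planned contrast and cannot simply replace it.

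**Conclusion.** The point holds. The planned set is fixed in the text and is one-sided, and the contrast it yields is not protected by randomisation, whatever the sign of any bias. Under a positive residual association it tends to favour e-Exercise: about 0.02 to 0.24 SD, with two-sided type I error about 0.05 to 0.29, for assumed adherent shares of 0.9 to 0.5 and correlations of 0.1 to 0.3. Only at low adherence and the higher correlations does the bias come near the lower end of the target effect. These sizes rest on assumed p and rho, 100 patients per arm and no clustering. The change is worth making, but the primary analysis does not depend on it.

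**What to change.** 1. Keep the planned contrast only as an exploratory, non-randomised analysis, say so in the text, and do not use p < 0.05 on it as evidence of effect.
2. Adjust it, or weight it by the inverse probability of adherence, using baseline predictors already collected: for example self-efficacy, education, pain, comorbidity, and baseline activity and function.
3. Add a complier-average causal effect analysis on all randomised patients, with allocation as instrument, a pre-set module count as exposure, baseline adjustment, and standard errors clustered on practice. It assumes that controls cannot reach the web programme; state this.
4. State the exclusion restriction openly and vary it, reporting the estimate after subtracting ((1 − p)/p) × tau_n over a pre-set range of tau_n on both sides of zero.

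The cost is revised wording, one extra model with a sensitivity analysis, and wider intervals. No new data are needed.
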